**EDUCATOR TRAINING & QUALITY ASSURANCE**

We will develop comprehensive educator training, quality assurance, and a development programme for Project STAND. This will be based on established protocols and infrastructure developed by the DESMOND collaborative [www.desmond-project.org.uk](http://www.desmond-project.org.uk/) (Davies 2008).

**PILOT STAND STRUCTURED EDUCATION COURSES**

Once developed, the course will be piloted with user groups and refined as required. Our group has previous expertise in the quality development of similar interventions (Skinner 2008, Yates 2008).Participants who meet the inclusion criteria outlined in Phase 1 will be recruited from primary care and the wider community. Participants will be recruited from the wider community using posters and media adverts. These will be distributed in supermarkets, Universities, hospitals etc. We will also approach large local companies within the Leicestershire region with a view to distributing posters and emails alerting their staff of the opportunity to participate in the study. They will attend a pilot STAND structured education course. At the end of the course information on the useful and less useful aspects of the course will be gathered from the participants (via questionnaires and interviews). This information will be used to refine the content and delivery of the course. Further pilot courses will be run until the research team are satisfied that the structured education course is fit for purpose.

**PHASE 3: RANDOMISED CONTROLLED TRIAL**

In Phase 3, the STAND group structured education course will be delivered in a randomised controlled trial to 178 participants from across Leicestershire and the South East Midlands Diabetes research network.

**HYPOTHESIS**

The primary hypothesis of the STAND randomised controlled trial is:

- Structured education can decrease sedentary behaviour in young adults at risk of T2DM

The secondary hypothesis is:

- Reduced sedentary behaviour results in favourable changes in key behavioural and biological markers of T2DM risk

**INCLUSION CRITERIA**

Participants who meet the following inclusion criteria will be recruited from primary care and the wider community:

Age 18-40 years plus a BMI ≥30kg/m2 (≥27.5kg/m2 for south Asians)

OR

Age 18-40 years with a BMI ≥25kg/m2 (≥23kg/m2 for south Asians) plus one of:

- - family history of diabetes or cardiovascular disease in a first degree relative;
  - previous gestational diabetes;
  - polycystic ovarian syndrome;
  - HbA1c ≥5.8% (from our local Addition Leicester diabetes screening data a cut off HbA1c of 5.8% provided the best sensitivity and specificity for a diagnosis of prediabetes).
  - Impaired glucose regulation

Defined according to the World Health Organisation as impaired glucose tolerance (2 hour glucose test from 7.8mmol/l to 11mmol/l following standard oral glucose tolerance test) *or* impaired fasting glucose (glucose value from 6.1 to 6.9mmol/l)

**EXCLUSION CRITERIA**

Due to the nature of the intervention, our exclusion criteria are as follows:

1. Physical condition which limits full participation in the study;
2. Active psychotic illness or a significant illness which, in the view of the investigators, would prevent full participation;
3. Inability to communicate in verbal and written English;
4. Steroid use;
5. Diabetes;
6. Pregnancy.

**RECRUITMENT: PRIMARY CARE**

Our initial strategy will be recruitment of participants from primary care, co-ordinated via the Primary Care Research Network (East Midlands and South Yorkshire (PCRN EMSY). Our group have established strong links with primary care, having recruited 8579 patients for ADDITION (Sandbaek 2008) in Leicester alone. We will use these existing links to recruit participants meeting the inclusion criteria (identified from GP data bases) from primary health care practices that reflect the diverse ethnic and socio-economic makeup of the Leicester, Northampton and Kettering regions. While we recognize that BMI is not routinely collected in some parts of the UK, there is a Locally Enhanced Service (LES) in place in Leicester City PCT that financially rewards individual practices for collecting BMI data, therefore BMI is now routinely captured in many primary health care practices within the region. We will recruit from up to 40 primary health care practices with an expected average list size of 6000 patients. Based on local practice records and census data we expect that about 10% of each practice population will meet our age range criteria, of which around 8-15% will meet the additional inclusion criteria given the high prevalence of diabetes and cardiovascular disease within the Leicester region. Based on previous research, we would expect that 20-30% of eligible individuals will consent to take part in the study. Practices will be recruited on an ongoing basis until the final sample size is reached. Around 30% of participants will be from a south Asian ethnic background, and 50-60% will be male.

Eligible individuals will be contacted by a member of their primary health care practice on behalf of our research team and invited to take part in the study. On agreement to take part they will be assigned a study number and identifiable data will be stored securely.

We will also contact Leicester ADDITION study participants who meet the inclusion criteria. Invitation letters will be sent to the participants. If interested, potential participants will return a reply slip to the research team. Research staff will send out the participant information sheet. Initial written contact will be followed by a telephone call to discuss participation and the details of the first study appointment.

**RECRUITMENT: SECONDARY CARE**

One of the study inclusion criteria is a family history of diabetes. As such we will send study information to patients with diabetes who are currently attending UHL diabetes services, to ask them to pass the study patient information sheet to relatives aged 18-40 years who may be interested in taking part in the study. We will also search UHL clinical workstation to identify patients attending the diabetes and endocrinology department who meet the inclusion criteria. Invite letters will be sent to patients who meet the inclusion criteria.

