**RANDOMISATION**

Once baseline data have been collected, participants will be randomised to either a control (C) or intervention (I) group, the latter being given the STAND structured education programme aimed at decreasing sedentary behaviour. Randomisation (stratified by age, sex, and ethnicity) will be set up by a statistician.

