**INTERVENTION ARM**

Each individual in the intervention arm will participate in the tailored, group, STAND structured self-management education programme which will be developed in Phase 2. The intervention programmes will be delivered by trained educators. It is envisaged that the courses will be delivered in a community setting, at a location considered convenient for the participants. Although the content has yet to be developed, Table 1 provides an example of how the STAND structured education course may look (based on the outline of the PREPARE programme). The detail of each module and the time dedicated to each will be informed by the work done in Phases 1 and 2. At the end of the education course the participant will be shown how to use the behaviour change technology which will provide ongoing personalised feedback on their sedentary time.

At 6 weeks, intervention arm participants will be contacted by study staff via telephone to review their progress to support behavioural change maintenance.

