**CONTROL ARM**

The control group will receive an information leaflet focusing on key illness perceptions of being at risk of T2DM, developed in the context of Leventhal’s common sense model. The leaflet will also focus on the importance of increasing physical activity and decreasing sedentary behaviour.

**Table 1:** Potential outline of the STAND structured education course which will be delivered to the participants in the intervention arm.

| **Module name** | **Main aims and educator activities** | **Theoretical underpinning** | **Time weighting** |
| --- | --- | --- | --- |
| ***Patient story*** | Give participants a chance to share their knowledge  and perception of sedentary behaviour in relation to diabetes risk and highlight any concerns  they may want addressed in the programme | Common sense model | 10%  (20 min) |
| ***Professional story*** | Use simple non-technical language, analogies, visual  aids and open questions to provide participants with  an overview of healthy glucose metabolism, the  aetiology of diabetes and the risk factors and  complications associated with diabetes  Help participants calculate their own individual  Diabetes risk scores | Common sense model  Dual process theory | 35%  (60 min) |
| ***Diet*** | Give participants an accurate understanding of the  link between diet and metabolic dysfunction | Social cognitive theory  Dual process theory | 15%  (25 min) |
| ***Sedentary behaviour*** | Use simple non-technical language, analogies,  visual aids and open questions to help participants:  identify how reducing sedentary behaviour may improve glucose control and body weight;  understand the current activity recommendations;  explore options for reducing sedentary behaviours in  everyday life; identify barriers to reducing sedentary behaviour; form action  plans and set personal goals  Practical demonstration of how to use the novel exercise technology for the self- regulation of sedentary time. | Social cognitive theory  Behavioural Choice Theory | 40%  (75 min) |

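### Relatives can be recruited through one patient and are randomised individually with no household rule, so a control may be exposed to the intervention at home

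*Protocol*

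**What the plan says.** Under Recruitment: Secondary care, the protocol explains that family history of diabetes is one of the inclusion criteria. It then plans to write to patients attending the hospital diabetes service "to ask them to pass the study patient information sheet to relatives aged 18-40 years who may be interested in taking part in the study". It sets no limit on how many relatives of one patient may join.

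Under Randomisation, the unit is the individual: "Once baseline data have been collected, participants will be randomised to either a control (C) or intervention (I) group". The only structure named is this: "Randomisation (stratified by age, sex, and ethnicity) will be set up by a statistician". Family and household are not mentioned.

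None of the six Phase 3 exclusion criteria bars a relative or housemate of someone already enrolled. Diabetes is an exclusion, so the patient who hands on the sheet cannot take part. The Sample size section makes no allowance for exposure of controls, and the Data analysis section does not mention related participants.

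The intervention arm receives group education, a telephone review at six weeks and "the behaviour change technology which will provide ongoing personalised feedback on their sedentary time". Controls receive a leaflet, of which the protocol says: "The leaflet will also focus on the importance of increasing physical activity and decreasing sedentary behaviour".

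**The concern.** The route through diabetes patients reaches families by design. The people it finds are likely to include siblings, or several adult children of one patient. Under equal individual allocation, a related pair is split about half the time.

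The Intervention design section aims to make less sedentary choices easier to reach and to limit some sedentary pursuits, and the example course outline in Table 1 includes a diet module. If a split pair shares a home, the control may take up some of this. Because the leaflet already tells controls to sit less, the contrast rests on the course, the follow-up call and the technology.

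Any such exposure shrinks the estimated effect on sedentary time and possibly on the diet- and weight-related secondary outcomes. The protocol describes this as a proof-of-concept trial whose success would lead to a larger one, so a diluted result is costly. An analysis plan could account for correlation within families, but it could not undo exposure that has already occurred. The rule has to be set before enrolment.

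**Working it through.** **Inputs from the protocol (Sample size).** Difference 5.67 hours/week, SD 12.1, Za = 1.96, Zb = 0.842, 72 per arm before dropout.

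**Reproducing the plan's figure.** N per arm = 2 × [(1.96 + 0.842) × 12.1 / 5.67]² = 71.5, rounded up to 72, which agrees with the protocol. At 72 per arm, SE = 12.1 × √(2/72) = 2.017, and power = Φ(5.67/2.017 − 1.96) = 80.3%.

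**Inputs the documents do not give (assumed).**
- s, the share of participants who belong to co-resident enrolled pairs: 5%, 10% or 20%.
- c, the share of controls with a co-resident relative in the intervention arm. Under 1:1 individual allocation the other member of a control's pair is in the intervention arm about half the time, so c ≈ s/2 = 2.5%, 5% or 10%.
- t, the share of the intervention effect passed on to such a control: 0.5 to 1.

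**Dilution.** d = 5.67 × (1 − c × t); power = Φ(d/2.017 − 1.96). The N that restores 80% power is 71.5 / (1 − c × t)², rounded up.

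| s | c | t | d (h/week) | Power at 72 per arm | N per arm for 80%, before dropout |
|---|---|---|---|---|---|
| 0 | 0 | – | 5.67 | 80.3% | 72 |
| 5% | 2.5% | 0.5 | 5.60 | 79.3% | 74 |
| 5% | 2.5% | 1 | 5.53 | 78.3% | 76 |
| 10% | 5% | 0.5 | 5.53 | 78.3% | 76 |
| 10% | 5% | 1 | 5.39 | 76.1% | 80 |
| 20% | 10% | 0.5 | 5.39 | 76.1% | 80 |
| 20% | 10% | 1 | 5.10 | 71.6% | 89 |

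The calculation covers dilution only and leaves correlation between relatives aside.

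**How large could the relatives route be?** Recruitment: Primary care gives up to 40 practices, lists averaging 6,000, about 10% in the age range, 8-15% of those eligible and 20-30% of those consenting:
- 40 × 6,000 × 10% = 24,000
- 24,000 × 8-15% = 1,920 to 3,600
- 1,920 × 20% = 384, and 3,600 × 30% = 1,080

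The trial needs 178. On the protocol's own estimate, primary care alone could fill it two to six times over, so the relatives route looks supplementary and the upper rows of the table are the more plausible ones.

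**The case against.** The strongest reply is that the problem may be very small. Primary care is the initial strategy, its projected yield exceeds the target, and there is also a community route. Family history is one of five alternative risk factors and is not needed at all at the higher BMI threshold. Adult siblings need not live together. The technology gives feedback on the wearer's own behaviour, controls already hold a leaflet on the same subject, and much sitting happens at work, where a relative does not share it. Any bias runs towards no difference, so it cannot manufacture a positive result.

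Most of this stands, and it limits the size of the point. It does not remove the gap: the protocol invites relatives and has no rule for them.

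A reader might infer more than the documents support:
- **Couples will be split between arms.** The route reaches relatives of a patient who is personally excluded. Siblings are the natural case, and nothing shows that couples will enrol.
- **Controls will be exposed at home, through a device used for the full 12 months.** Neither co-residence nor a period of device use is stated. Exposure is possible, not established.
- **Power could fall to about 61%.** That needs 20% of controls affected and the whole effect passed on (d = 5.67 × 0.80 = 4.54). Since only about half of pairs are split, some 40% of all participants would have to be in co-resident pairs. Even 10% of controls affected implies 20% of participants in such pairs, so it is used here as an upper bound.

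**Conclusion.** The point holds in a limited form. The protocol recruits relatives without a limit per family and randomises individuals without a household rule, so co-resident relatives may be divided between arms and a control may be exposed to the intervention. The bias would be towards zero.

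Its size cannot be derived from the protocol. Over the assumed range above, the loss runs from 1 to about 9 percentage points of power; with 5% of participants in pairs it is 1-2 points. This is a worthwhile, inexpensive improvement to the design, not a flaw that threatens the trial.

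**What to change.** State in the Phase 3 inclusion criteria, and repeat under Recruitment: Secondary care, that only one participant per household is enrolled. Ask about shared address and participating relatives at the first study appointment. The rule should apply to every recruitment route. This costs one sentence and one screening question, plus a few willing relatives turned away from a group the protocol itself regards as hard to recruit. The projected primary-care yield suggests that loss can be absorbed.

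Do not give later household members the allocation of the first. Their arm would be known before they consent, which breaks concealment, and the design would acquire clustering that neither the sample size nor the analysis now handles.

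If co-enrolment is to be allowed, identify all joining members of a household before allocation, randomise them together as one unit, record the household, and account for the clustering in the analysis.

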**RECRUITMENT: COMMUNITY**

Participants will be recruited from the wider community using posters and media adverts. These will be distributed in supermarkets, Universities, hospitals etc. We will also approach large local companies within the East Midlands region (Leicestershire, Nottinghamshire, Derbyshire etc) with a view to distributing posters and emails alerting their staff of the opportunity to participate in the study. Potential participants will contact the research team directly. We will send them the participant information letter and they will have at least a week to decide whether they wish to participate. If they are agreeable, an appointment will be made for the first study visit.

All study participants will be fully reimbursed for their travelling expenses. In addition, we recognise that our target group are a hard to reach group with many pressures on their time (work, family etc). Therefore, we will provide participants with £20 for each study visit (1/2 day per visit) as a token of appreciation of their time.

**RANDOMISATION**

Once baseline data have been collected, participants will be randomised to either a control (C) or intervention (I) group, the latter being given the STAND structured education programme aimed at decreasing sedentary behaviour. Randomisation (stratified by age, sex, and ethnicity) will be set up by a statistician.

**INTERVENTION ARM**

Each individual in the intervention arm will participate in the tailored, group, STAND structured self-management education programme which will be developed in Phase 2. The intervention programmes will be delivered by trained educators. It is envisaged that the courses will be delivered in a community setting, at a location considered convenient for the participants. Although the content has yet to be developed, Table 1 provides an example of how the STAND structured education course may look (based on the outline of the PREPARE programme). The detail of each module and the time dedicated to each will be informed by the work done in Phases 1 and 2. At the end of the education course the participant will be shown how to use the behaviour change technology which will provide ongoing personalised feedback on their sedentary time.

At 6 weeks, intervention arm participants will be contacted by study staff via telephone to review their progress to support behavioural change maintenance.

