**SAMPLE SIZE**

The primary outcome of the intervention trial will be reduced sedentary behaviour, measured by an accelerometer (time <100 counts/min as assessed by 1-week accelerometry) at 12 months. The minimum reduction in sedentary behaviour that would yield beneficial metabolic effects has not been determined. Cross-sectional data suggests that each 10% increase in sedentary time is associated with a 3.1cm increase in waist circumference, and that sedentary time is positively associated with clustered metabolic risk (Healy 2008). Using the same dataset, the mean sedentary time is 56.7 hours/week. Therefore, we suggest that a minimum clinically important difference would be 5.67 hours/week, reducing to 51.03 (SD 12.1). Sample size is estimated as 2N = (4(Za+Zb)2s2)/d2 (where d is the true between-arms difference, b is the type II error rate, and a is the type I error rate). Alpha is set at P = 0.05 (Za = 1.96) and power at 80% (b = 0.20, Zb =.842). This results in a required N of 72 in each arm. Incorporating a drop out rate of 25% gives a final N of 89 per arm.

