**PROCESS EVALUATION**

Process evaluation will explore the implementation, delivery, context and reach of our STAND intervention. It will also allow us to develop and understanding of its impact on various sub-groups. The questions we wish to address are:

- What is the relation between trial outcome and variation in the extent and quality of the implementation of the intervention?
- What processes mediate the relation between intervention and outcomes?
- Do subgroups (e.g. age, ethnicity etc) differ in their responses to the intervention?

This process will involve quantitative and qualitative methods: questionnaire surveys, focus groups, interviews, researcher observations, and structured field notes during the delivery of the intervention. The identification of key mediating factors will facilitate later understanding and interpretation of the STAND intervention outcomes. Once 1 year follow up data have been collected we will have the opportunity to perform quantitative analysis of the impact of our intervention on various sub-groups (e.g. ethnicity) and mediators (e.g. course educators, location). By integrating our process and outcome data we will be able to develop a fuller understanding of our intervention components (Oakley 2006). This process will allow us to identify the relative merits of the intervention concept/theory and delivery/implementation (Rychetnik 2002).

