**DATA ANALYSIS**

The study will be reported according to the CONSORT statement for randomised control trials. Data will be analysed on an intention-to-treat basis (ITT). Data will be analysed using STATA v10 and SPSS v16 software. Descriptive statistics (mean values and frequencies) will be calculated. Histograms will be used to identify any outliers and to test for normality. Robust ANCOVA modelling will be used to look at the difference between groups in change in continuous outcome measures and logistic regression will be used to analyse categorical variables. Results will be disseminated via peer-reviewed publications and presentations at national and international meetings.

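### Group delivery in the intervention arm only is not allowed for in the sample size, and the stated ANCOVA names no education-group term

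*Protocol*

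**What the plan says.** Protocol, Randomisation: individual participants are allocated, stratified by age, sex and ethnicity.

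Protocol, Intervention Arm: "Each individual in the intervention arm will participate in the tailored, group, STAND structured self-management education programme". Trained educators deliver it, with community venues envisaged. Under Control Arm, the comparator is an information leaflet, so treatment creates no grouping there.

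Protocol, Sample Size: "Sample size is estimated as 2N = (4(Za+Zb)2s2)/d2", with "Alpha is set at P = 0.05 (Za = 1.96) and power at 80" per cent and "a minimum clinically important difference would be 5.67 hours/week, reducing to 51.03 (SD 12.1" as the effect and spread. "This results in a required N of 72 in each arm", and then "Incorporating a drop out rate of 25% gives a final N of 89 per arm". No group size, ICC or design effect appears.

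Protocol, Data Analysis: "Robust ANCOVA modelling will be used to look at the difference between groups in change in continuous outcome measures". The covariates are not listed, the word robust is not explained, and education group and educator are not mentioned.

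Protocol, Process Evaluation: once one-year data are in, there will be an opportunity to look at "mediators (e.g. course educators, location" and similar factors.

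**The concern.** People who attend the same course share a session, an educator, a venue and each other. The course outline relies on this: participants share their views, explore options, and form plans and goals in the session. Their 12-month sedentary time may therefore be correlated in a way that the leaflet arm's is not. This is a partially nested design, with one arm clustered and the other not.

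Two things are at stake. The first is the power claim, because the formula used is correct only for independent observations. The second is the precision of the primary result, because a model that left out education group would understate the variance of the intervention-arm mean.

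**Working it through.** **Inputs from the protocol (Sample Size).** Difference d = 5.67 h/week; SD s = 12.1 h/week; two-sided alpha 0.05 (1.96); power 80% (0.842); 72 evaluable per arm.

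**Inputs not in the protocol, assumed here.** Analysed participants per education group, m = 5, 8 or 10. ICC = 0.01, 0.02 or 0.05. The total SD is taken as 12.1 in both arms. A normal approximation is used.

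**Step 1. Reproduce the plan's figure.** Per arm, N = 2 × (12.1 × 2.802 / 5.67)² = 71.5, so 72. This agrees. With 72 independent participants per arm, SE = 12.1 × √(2/72) = 2.017 and power = Φ(5.67/2.017 − 1.96) = 80.3%.

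**Step 2. Allow for clustering in the intervention arm only.** The design effect in that arm is DE = 1 + (m − 1) × ICC. Then SE = 12.1 × √((1 + DE)/72) and power = Φ(5.67/SE − 1.96). For m = 8 and ICC = 0.05, DE = 1.35, SE = 12.1 × √(2.35/72) = 2.186, and power = Φ(0.634) = 73.7%.

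**Step 3. Size of the error if education group were ignored.** The ratio of the naive to the correct SE is √(2/(1 + DE)).

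| m | ICC | DE | Power, 72 per arm | Naive SE ÷ correct SE |
| --- | --- | --- | --- | --- |
| 5 | 0.01 | 1.04 | 79.5% | 0.990 |
| 5 | 0.02 | 1.08 | 78.7% | 0.981 |
| 5 | 0.05 | 1.20 | 76.4% | 0.953 |
| 8 | 0.01 | 1.07 | 78.9% | 0.983 |
| 8 | 0.02 | 1.14 | 77.6% | 0.967 |
| 8 | 0.05 | 1.35 | 73.7% | 0.923 |
| 10 | 0.01 | 1.09 | 78.5% | 0.978 |
| 10 | 0.02 | 1.18 | 76.8% | 0.958 |
| 10 | 0.05 | 1.45 | 71.9% | 0.904 |

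Clustering alone therefore costs between 0.8 points (80.3 − 79.5) and 8.4 points (80.3 − 71.9).

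**Step 4. Possible offset from baseline adjustment.** The formula takes no credit for it. If the model adjusts for baseline with correlation r to the 12-month value, replace s by 12.1 × √(1 − r²), and apply the ICC to what remains. For m = 8 and ICC = 0.05 at 72 per arm:

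- r = 0.3: s = 11.54, SE = 2.085, power about 78%.
- r = 0.5: s = 10.48, SE = 1.893, power about 85%.

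Both correlations are assumptions. The factor √(1 − r²) cancels in the ratio of Step 3, so the adjustment does not correct the interval.

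**Step 5. Keep the dropout arithmetic apart.** The stated 89 is 71.5 × 1.25 = 89.4, rounded down. Allowing for a 25% loss requires 72/0.75 = 96. With 89 recruited, 89 × 0.75 = 66.75 remain, and power is 77.3% with no clustering at all. That fall from 80% to 77% is a separate error and is not part of the clustering loss above.

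**The case against.** The strongest objection concerns the analysis. A reader might infer that the ANCOVA treats all participants as independent, so that the reported interval is bound to be too narrow. The protocol does not say so. Robust is undefined and could mean standard errors clustered by education group. The statistical analysis plan, where such detail usually sits, is not at hand. This objection stands: all that can be said is that the model as written names no education-group term.

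The power loss is also conditional. It needs an ICC above zero, both the ICC and the group size are assumed, and baseline adjustment could restore 80%. This stands too, with the caveat that baseline adjustment is itself an inference, since the covariates are not listed. It does not rescue the formula, which is printed in the protocol and takes no account of the design described there.

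A reader might further infer an inflated type I error for the primary and every secondary outcome. If the programme affected nobody, attending a course would create no such correlation, and the naive test would keep about its nominal level. Over the range above, the rate would be about 5.2% to 7.7%, but only if education groups shifted outcomes in directions that averaged to zero and the analysis ignored education group. No ICC is available for the secondary outcomes.

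Finally, the Process Evaluation section only plans to explore educators and location. It does not say that they will influence outcome. That educators each run several courses is likewise inferred. Neither is needed here, because attending the same session is enough to create the correlation.

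**Conclusion.** The point holds in a conditional form. The sample-size section uses a formula for independent participants in a trial where one arm is taught in groups, so for any positive ICC its 80% is too high on the section's own terms. For 5 to 10 analysed per education group and an ICC of 0.01 to 0.05, power at 72 per arm is 79.5% down to 71.9%. The loss is trivial at the low end and material at the high end. An analysis that ignored education group would have a standard error about 1% to 10% too small. Whether the planned analysis ignores it cannot be settled from the protocol.

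The documents do not support saying that 80% power will certainly be missed: at 8 per education group and an ICC of 0.05, a baseline correlation of 0.5 would give about 85% at 72 per arm. It is worth changing because the remedy is cheap and protects the primary interval.

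**What to change.** 1. Record each participant's education group and educator at delivery, as planned data items. This is easy at the time of the course and may be hard to reconstruct later.
2. In Data Analysis, state that the primary model accounts for education group in the intervention arm, with controls treated as singletons. A partially nested mixed model would do this, as would cluster-robust standard errors with a small-sample correction. The correction matters because the groups are few: 72 participants in groups of 8 make only 9.
3. In Sample Size, restate power over a range of assumed ICCs and group sizes, and say what baseline correlation is assumed if credit is taken for adjustment. Deal with the dropout inflation separately.

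This point alone does not require a change to the total of 178. The cost is a few lines of text and two recorded variables. The downside is a slightly wider interval and a less favourable stated power.
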